#### Control intervention

Participants in the control group will be advised at baseline to keep their lifestyle habits unchanged. With the second measurements at the final appointment, they will receive a similar training schedule as the participants in the intervention period for self-administered training and also standard recommendations regarding physical activity and a healthy lifestyle, based on the WHO’s guidelines for physical activity [79].

## Discussion

### Strengths and limitations – participant recruitment

Selection bias can occur, since invitation letters will be distributed in an anonymous fashion in the Basel region. Therefore, selection of candidates who are motivated to improve their health via training is likely, while missing those with lower level of motivation. Hence, limited assertion can be made regarding training adherence in association with the participants’ state of motivation. No statement can be made about effects of NLPE on endothelial function in other populations, such as women, children and patients with cardiovascular disease and ethnicities. Although, the effects might be similar, further projects involving the respective target populations will be necessary before conclusions can be drawn.

### Strengths and limitations – training intervention

Due to the nature of training intervention studies, participant compliance and adherence during the intervention period constitutes another source of potential bias. Compliance and mental status will be assessed using the Profile-of-Mood-States questionnaire. In combination with the drop-out-rate, expectations can be made about adherence to this new training regimen. Yet, based on previous experience of the investigators and others [80], a 10% drop-out rate is expected due to lack of compliance or adverse events, such as infections or injuries during the intervention period which may result in missing more than 10% of training time or even incapability to continue the study participation.

Moreover, the strict adherence to target intensities and overall training load is important for reliable measurement outcomes. Externally controlled ergometer bicycles will be used during the supervised training sessions, with a personalized intensity preset for every training session. Cardiorespiratory fitness will be reassessed after four weeks of training to adjust individual target intensities. Thereby, training in the target intensities throughout the whole intervention period will be assured.

Finally, to ensure valid effect estimates of the outcome parameters, all participants who completed less than 90% of the sessions at the predefined intensity will be excluded from the study. To avoid attrition bias, data acquired until drop-out will be included in the statistical analyses.

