### Methods and measurements

Measurements will be conducted during a three-to-four-hour appointment within two weeks before the start of the intervention (baseline appointment) and within three to seven days after the final training session (final appointment). After four weeks of training, another spiroergometric measurement of cardiorespiratory fitness will be conducted to adjust the target training intensities to the current progress of the individual fitness level [80] (Table 1). To ensure equal testing conditions and optimal data quality, all measurements will be conducted according to standardized operating protocols based on current guidelines and the assessment staff will undergo a rigorous training of all methods before the start of participant recruitment.

**Table 1 Tab1:** Outcomes assessed in the VascuFit study

Outcome measure	Data collection instrument	Telephone interview	Baseline appointment (T_0_)	Fitness check (T_1_)	Final appointment (T_2_)
Inclusion criteria ^a^	Questionnaire (5 items)	x			
Exclusion criteria ^a^	Questionnaire (8 items)	x			
Physical activity readiness	PAR_Q (7 items)		x		
Physical activity	PA_Q (41 items)		x		
General well-being	POMS (19 items)		x		x
General health	Medical interview ^b^, physical examination		x		x
Body composition	^BMI, bioelectrical impedance analysis^		x		x
Cardiovascular function	BP, heart rate, ECG at rest and during exercise		x	x	x
Macrovascular endothelial function	baFMD		x		x
Microvascular endothelial function	SVA		x		x
Molecular endothelial function	endomiRs (15 species)		x		x
Cellular endothelial function	ECs, EPCs		x		x
Circulating cardiovascular risk factors	fasting blood glucose, LDL-, HDL- and total cholesterol, triglycerides, hs-CRP, sphingolipidome		x		x
Pulmonary function	Spirometry		x		x
Cardiorespiratory fitness	Spiroergometry with breath-by-breath gas analysis and capillary blood lactate		x	x	x

^a^ See methods section for details, ^b^ Medical interview including general health, chronic diseases, lifestyle and family history of cardiovascular diseases (14 items) and current medication (2 items per drug)

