#### Training intervention

The training will be conducted under supervision by experienced exercise coaches with at least a Bachelor’s degree in sports science. It will be conducted in groups of up to nine participants and will begin no more than two weeks after the baseline appointment.

The NLPE intervention will consists of two macrocycles of four weeks each, and the second cycle will be more intense than the first one. Every week, participants will attend three training sessions varying in duration and intensity. After the completion of the first macrocycle, another spiroergometry testing will be performed to readjust the intensity for the following training sessions. The exact amount of this increase will be defined individually for every participant according to their performance development (V̇O2_peak_ at T_1_) as well as individual readiness and appreciation assessed during the intervention period. This will ensure training in the target intensities throughout the whole study period and thus avoiding a common methodological limitation of many exercise trials.

Each session will start with a 15-min warm-up to minimize the risk of injury during training [112, 113]. Exercises for strength, dynamic flexibility and balance will also be included, which further support the training performance [114] and improve neuromuscular control [112]. In weeks 1 (habituation) and 5 (recovery), each session will consist of 30 min continuous cycling at moderate intensity of 40 – 50% peak oxygen consumption (V̇O2_peak_). Comparing to weeks 1 and 5, cycling duration will be longer in weeks 2 and 6 (high-volume for metabolic adaptation, i.e., mitochondrial density, improved anti-oxidant capacities) and intensities will be higher in weeks 3 and 7 (high-intensity for structural adaptation, i.e., remodeling of the extracellular matrix in the vascular wall). In weeks 4 and 8, both cycling duration and intensities will be higher (peak performance enhancement).

To ensure an adequate wash-out period without risking a loss of training effect, the final appointment, including another spiroergometry test of cardiorespiratory fitness, will take place three to seven days after the last training session. The participants will then receive standard recommendations regarding physical activity and a healthy lifestyle, based on the WHO’s guidelines for physical activity [79].

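### Excluding participants with under 90% of sessions at target intensity can remove only NLPE participants after randomisation, so it can bias the primary comparison, and keeping data up to drop-out does not protect baFMD

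*Protocol article*

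**What the plan says.** In the Discussion of the protocol article, under Strengths and limitations – training intervention, the rule is that "all participants who completed less than 90% of the sessions at the predefined intensity will be excluded from the study". Its stated purpose is to secure valid effect estimates. The next sentence adds: "To avoid attrition bias, data acquired until drop-out will be included in the statistical analyses". The same section says "Compliance and mental status will be assessed using the Profile-of-Mood-States questionnaire". It expects 10% drop-out, and that figure already includes people who miss more than 10% of training time through poor compliance, infection or injury.

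The section Training intervention describes "two macrocycles of four weeks each" and states: "Every week, participants will attend three training sessions varying in duration and intensity". For the other arm, the section Control intervention says: "Participants in the control group will be advised at baseline to keep their lifestyle habits unchanged". Controls get a schedule only at the end: "With the second measurements at the final appointment, they will receive a similar training schedule".

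Table 1 places baFMD, retinal vessel analysis, endomiRs and the endothelial cell counts at T0 and T2 only. The T1 visit covers spiroergometry, blood pressure, heart rate and ECG. The Statistical analyses section names paired t-tests within groups and ANCOVA between groups.

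**The concern.** Randomisation makes the two arms comparable at the start. A rule that removes people for what happens afterwards keeps that comparability only if removal is unrelated to outcome or works alike in both arms. Here it works in one arm only. The article's own reasons for missed training are poor compliance, infections and injuries. NLPE participants with these problems would leave the comparison, while similar people in the control arm would stay.

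If those who train reliably would also have had better baFMD at T2 for other reasons, part of the observed difference would be selection and not training. The rule would then work against the purpose given for it. The primary outcome is at stake, in a trial of 43 people where each exclusion counts. The sentence on attrition bias looks like a safeguard, but for baFMD it depends on a T2 value that an excluded participant may not have.

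**Working it through.** **1. The threshold.** 8 weeks × 3 sessions = 24 sessions, and 0.90 × 24 = 21.6. A participant needs 22, so a third missed or off-target session leads to exclusion. Controls have 0 sessions before T2, so none can fail.

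**2. The plan's own sample size.** The plan needs 39 evaluable (26 + 13) and recruits 43 for 10% drop-out. 39 × 1.1 = 42.9, which rounds up to 43. 39 / 0.9 = 43.3 would round up to 44, so the stated figure is reproduced to within one participant. The arms become 28 and 15. The NLPE arm can lose two (2/28 = 7.1%) before falling below 26. The control arm can also lose two (2/15 = 13.3%), though the rule cannot touch it.

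**3. How many might be excluded.** The article gives no per-session compliance, so this is an assumed range with independent sessions. P(excluded) = P(X ≤ 21), with X binomial(24, p).

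| p per session | Share excluded | Expected of 28 | P(more than 2 of 28) |
|---|---|---|---|
| 0.97 | 3.4% | 1.0 | 7% |
| 0.95 | 11.6% | 3.2 | 65% |
| 0.90 | 43.6% | 12.2 | >99% |

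Holding exclusion to 10% needs p of about 0.953.

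**4. What the safeguard leaves.** Someone removed without a T2 visit has one baFMD value, at T0. The paired t-test needs T2 minus T0 and the ANCOVA needs T2 as its response, so that person adds nothing to either. The same holds for the other outcomes measured only at T0 and T2. V̇O2peak, blood pressure and heart rate do have a T1 value that could be kept.

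**5. The SD.** None is stated. Solving for it from 26 + 13, a difference of 2.67 points, r = 0.60, two-sided 5% and 80% power gives 3.51 (normal approximation) or 3.41 (t-based). The residual SD is SD × √(1 − 0.60²) = 0.8 × SD, so 3.51 gives 2.81.

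**6. Illustrative bias with no true effect.** Suppose a latent adherence variable has correlation ρ with the ANCOVA residual, and the lowest fraction f of the NLPE arm is removed. The mean residual of those who remain rises by

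bias = ρ × φ(z_f) / (1 − f) × residual SD.

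For f = 0.10, φ(z_f)/(1 − f) = 0.195. With ρ = 0.3, bias = 0.3 × 0.195 × 2.81 = 0.16; with ρ = 0.5 it is 0.27. For f = 0.20 the factor is 0.350, which gives 0.29 and 0.49.

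| NLPE excluded | ρ | Spurious benefit (points) | Share of 2.67 | Simulated type I error |
|---|---|---|---|---|
| any | 0 | 0 | 0% | about 5% |
| 10% | 0.3 to 0.5 | +0.16 to +0.27 | 6 to 10% | about 5 to 6.5% |
| 20% | 0.3 to 0.5 | +0.29 to +0.49 | 11 to 18% | about 6 to 9% |

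Type I error comes from simulated ANCOVAs with 28 and 15 randomised and exclusion in the NLPE arm only.

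**7. Power if everyone is analysed as randomised.** With 28 and 15, and SD 3.41 to 3.51:

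| NLPE participants not adhering | Their gain | Mean effect | Power |
|---|---|---|---|
| 0% | – | 2.67 | 83 to 85% |
| 10% | half | 2.67 × 0.95 = 2.54 | 79 to 81% |
| 10% | none | 2.67 × 0.90 = 2.40 | 74 to 77% |
| 20% | none | 2.67 × 0.80 = 2.14 | 64 to 67% |

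**The case against.** The best defence is that the trial is a proof of concept. It asks whether NLPE works when it is actually performed, and the article leaves feasibility and compliance to later trials. The 10% allowance already covers missed training, and supervised sessions on externally controlled ergometers should keep compliance high. Infections and injuries need not be related to baFMD response. At the planned 10% loss the illustrated bias is small.

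Much of this limits the size of the problem. None of it makes a one-sided exclusion safe: an effect among adherers also needs an account of selection, and the article states none.

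A reader might go further than the document allows in four ways.

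- The exclusion and data-retention sentences might be read as a contradiction. They can be read together: the participant is withdrawn and earlier data are kept. The weakness is that the earlier data are of no use for baFMD.
- The safeguard might be called empty throughout. The article does not say whether an excluded participant still attends T2, and three measures have a T1 value.
- The NLPE arm might be said to end below 26. That happens only if more than two of 28 are excluded.
- A large bias might be inferred from low attendance. Very high exclusion combined with strong correlation would produce one, but the document supports neither assumption.

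**Conclusion.** The concern holds in this form. The article fixes a post-randomisation exclusion that only the NLPE arm can fail, and it can bias the primary between-group comparison. A bias in favour of NLPE is plausible but not proven. The rule does not secure valid estimates, and keeping data up to drop-out gives no protection for outcomes measured only at T0 and T2 when there is no T2 visit.

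The 22-of-24 threshold, its one-sidedness and the margin of two NLPE losses follow directly from the document. The size of the bias does not: it depends on the back-solved SD, the assumed correlation and the fraction removed. At the plan's own 10% loss it is modest, and it grows if exclusions exceed that. The point should be settled before analysis because the rule decides who enters the primary comparison.

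**What to change.** - Remove the 90% rule from the primary analysis.
- Invite every randomised participant to T2 whatever their attendance.
- Analyse all participants in the arm to which they were randomised, with a stated sensitivity analysis for any missing T2 baFMD.
- Keep the set with 90% or more of sessions as a labelled per-protocol sensitivity analysis.
- Report adherence from session attendance and ergometer load. A mood questionnaire measures neither.
- Recheck the stated 80% power for the as-randomised analysis, or restate it.

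The practical cost is small: a change of wording, and T2 visits for low attenders. The article already plans 86 endomiR samples, which is 43 × 2, so a second sample from everyone is foreseen. The statistical cost is dilution of the effect, with power as low as 74 to 77% in the case of 10% non-adherence with no gain. That should be stated openly.

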### Strengths and limitations – outcome measurements

Measurement of baFMD is very sensitive to investigator bias and to bias introduced by unstable environmental and situational conditions. An extensive training of the assessment staff before the start of measurements as well as strict adherence to detailed standardized operating procedures based on current guidelines [84] is crucial for valid results. Furthermore, the software-based semi-automatic quality control of baFMD measurements will be conducted by a trained person who will be blinded to the group allocation of the cases.

Although the measurement of SVA is less sensitive to investigator bias, the post-procedural manual quality control of the pictures, including the measurement of arteriolar and venular diameters, will also be made by an experienced assessor following standardized procedures [115].

To counteract the circadian, seasonal, and hemodynamic fluctuations that influence both clinical and molecular outcome measures, every measurement will be made under similar conditions (resting time, daytime, fasted, room temperature). However, seasonal fluctuations are imaginable. Hence, the effects could be slightly different, if the study was conducted in winter. However, this bias is most likely negligible with regards of the primary outcome, which is the “before-after” difference of the outcome parameters with “before” and “after” measurements being conducted within 2.5 months.

Thus far, only few studies have assessed effects of exercise on endomiRs, ECs, EPCs and sphingolipidome. In fact, there is no study assessing the effects of NLPE on these markers. However, the selection of target biomarkers and processing of samples brings various challenges and can ultimately lead to heavily flawed data and unreliable results. Most importantly, sample acquisition and processing need to be conducted timely and without any contamination, as pre-processing of serum for endomiR analysis can only be made within the first 60 min after sample acquisition.

Circulating miRNAs are promising biomarkers to provide unprecedented precision and resolution of monitoring and guidance of exercise that aims to improve cardiovascular health. Although several studies more or less successfully sought to identify single miRNAs that might serve this purpose, this approach is prone to considerable bias due to a high technical variability in the absence of adherence to strict procedural and technical standards [56]. Furthermore, single miRNAs have a high biological variability. An appropriate number of biological replicates and normalizer miRNAs, depending on the protocol used, and also controlling for sample volume will minimize the biological variability. To further reduce the possibility of an incidental finding, the VascuFit study will not analyze changes of serum levels of few single miRNAs, but assess the change of pattern in a whole set of selected miRNAs. Although these circulating miRNAs have been selected based on in vitro and in vivo evidence indicating a key role in the regulation of endothelial cellular metabolism and sensitivity towards endothelial shear stress, a selection bias cannot be ruled out entirely.

Furthermore, evidence indicates that changes in circulating miRNAs due to chronic exercise might not lead to different serum levels at rest but to a more distinct change after an acute bout of exercise [116]. Thus, measuring the serum levels of miRNAs only before exercise testing in a rested state might lead to non-significant results without clearly indicating adaptive non-response to the training.

### The potential of non-linear periodized aerobic exercise (NLPE)

Successful exercise medicine requires two major ingredients: first, a training method that is flexible enough to target the specific needs of the trainee and second, biomarkers for a precise monitoring of training success and adaptation of the training regimen to optimize effectiveness of the treatment.

The VascuFit project is designed to introduce a flexible method for aerobic exercise, NLPE, and to demonstrate proof-of-concept for its applicability in the general sedentary population. Therefore, the primary aim will be to assess changes of established biomarkers of clinical vascular function associated to the training.

This study will demonstrate whether NLPE can improve baFMD, the gold-standard biomarker of macrovascular endothelial function. It will also indicate whether SVA, a biomarker of microvascular endothelial function, may be improved by NLPE as well. Combining both outcomes, VascuFit may provide evidence about differences/ similarities of different local vascular beds in their responsiveness to aerobic exercise. As both measurement sites are not involved in the main training area, the results can, at least partly, be taken as surrogates for systemic vascular effects of NLPE. Future projects may build on the study results by translating them on other populations, such as women, children, very old healthy subjects or patients with cardiovascular or other diseases. The applicability of NLPE in therapeutic settings cannot be determined by this single proof-of-concept study. Accordingly, further trials need to be designed in a way that allows to obtain evidence about feasibility, effectiveness, compliance and appreciation of NLPE in a clinical setting. As the training regimen in the VascuFit project is relatively fixed, especially the effectiveness in terms of improved cardiorespiratory fitness needs to be proven in a more flexible setting. Only if there is a high degree of individuality added to the training, conclusions can be drawn on whether NLPE truly fulfills its promise of a more personalized method than common methods, e.g., HIIT or MICT.

### The potential of clinical and molecular biomarkers of endothelial function

The change of a single biomarker never tells the entire story. Exercise intervention trials deliver controversial evidence, with some demonstrating an improved baFMD and others finding no changes [43, 117, 118]. Therefore, additional biomarkers are necessary that promote the understanding of the exact mechanisms underlying endothelial adaptations to exercise. As such, changes of molecular biomarkers of endothelial cellular composition, including endomiRs as well as ECs and EPCs, may help identify potential candidates for a more precise and efficient monitoring and guidance of training interventions that aim to improve and maintain good vascular health.

By targeting a select set of specific endomiRs which regulate key molecular pathways of endothelial function, instead of analyzing few single miRNAs, VascuFit intends to overcome common limitations of such molecular biomarkers, e.g., their large inter- and intra-individual variability. The selected miRNAs share important common traits: a) they are all abundantly expressed in endothelial cells and their target proteins have been identified in mechanistic studies of human models; b) they are secreted into the blood, thus measurable in the serum; c) they are mechanosensitive, thus susceptible to hemodynamic adaptive stimuli of exercise, just as baFMD. Accordingly, an association between these molecular biomarkers and the clinical indicators of vascular aging, baFMD and SVA, might support the understanding of the underlying molecular processes of endothelial adaptations towards exercise stimuli. However, causality cannot be established based on these results without providing a full picture of all subsequent steps from epigenetic modifications induced by the selected miRNAs over transcription, translation and cellular metabolic cascades towards the clinical observation. Yet, the identification of a set of miRNAs highly sensitive to exercise stimuli and closely correlated to changes of the clinical biomarkers may lay ground for further clinical and also molecular in vivo and in vitro studies.

